## Abstract

**Background:** People experiencing homelessness and mental illness have poorer service engagement and health-related outcomes compared to the general population. Financial incentives have been associated with increased service engagement, but evidence of effectiveness is limited. This protocol evaluates the acceptability and impact of financial incentives on service engagement among adults experiencing homelessness and mental illness in Toronto, Canada.

**Methods:** This study protocol uses a pragmatic field trial design and mixed methods (ClinicalTrials.gov Identifier: NCT03770221). Study participants were recruited from a brief multidisciplinary case management program for adults experiencing homelessness and mental illness following hospital discharge, and were randomly assigned to usual care or a financial incentives arm offering $20 for each week they attended meetings with a program provider. The primary outcome of effectiveness is service engagement, measured by the count of participant-provider health-care contacts over the 6-month period post-randomization. Secondary health, health service use, quality of life, and housing outcomes were measured at baseline and at 6-month follow-up. Quantitative data will be analyzed using descriptive statistics and inferential modeling including Poisson regression and generalized estimating equations. A subset of study participants and other key informants participated in interviews, and program staff in focus groups, to explore experiences with and perspectives regarding financial incentives. Qualitative data will be rigorously coded and thematically analyzed.

**Conclusions:** Findings from this study will contribute high quality evidence to an underdeveloped literature base on the effectiveness and acceptability of financial incentives to improve service engagement and health-related outcomes among adults experiencing homelessness and mental illness.

## Introduction

People experiencing homelessness and mental illness have significantly poorer mental and physical health and quality of life relative to the general population (1–3). In addition, compared to the general population, they have higher rates of acute care utilization and associated costs (2, 4, 5). Efforts to improve the health and health service use outcomes of this population have historically been challenged by poor service engagement and high drop-out rates (6). Lack of service engagement has in turn been associated with poor health outcomes, including increased symptom severity, reduced quality of life, a greater likelihood of returning to hospital (6–8), and increased acute care costs (6, 7). Strategies to improve service engagement are essential to maximizing treatment effectiveness and to improving the health and social outcomes of this population.

For adults experiencing homelessness and mental illness, the transition from hospital to community settings has been associated with an increased risk of homelessness (9) and worsened mental illness (10). Programs and interventions aiming to support this population in establishing (re)connections to housing and community-based resources during care transition, such as Critical Time Intervention, have been used successfully to improve the health (11), health service use (12–14), quality of life (11, 14), and housing outcomes (9, 15) of this population. Further research, focused on practical strategies to improve service engagement, particularly in the critical period following hospital discharge, is essential to maximizing the impact of such interventions and to improving health and social outcomes in this population.

An individual's decision to engage in and adhere to treatment is influenced by a wide range of factors. Behavioral economics principles in health care suggest that individuals have a tendency to make health decisions that are biased toward the present and immediate rewards vs. future outcomes and delayed gratification (16, 17). These principles have been used in intervention design to motivate individuals to make health-promoting decisions, including engaging in treatment or services (18). Literature on interventions to promote service engagement among people experiencing mental illness has suggested that the provision of practical housing and financial supports are important in promoting service engagement (19, 20). It has also been proposed that financial incentives, providing a reliable, practical, and immediate reward for health-promoting behaviors, may be an effective engagement strategy and positively influence health decision-making, and consequently improve health and health service use outcomes in vulnerable populations (18, 21–24).

Financial incentives have indeed been shown to influence health behaviors for a range of health conditions, including increasing smoking cessation rates (25, 26), weight loss (27), engagement in HIV care and prevention (28–30), blood donation (31), and adherence to tuberculosis treatment (32). Reviews of the literature have found that financial incentives were effective in 73% of cases (33), and that effects were greater for singular behaviors compared to complex, sustained behavior change (33) and for shorter-term (<6 months) interventions (22). Specifically among people experiencing homelessness and/or mental illness, financial incentives have been shown to improve health outcomes such as therapy adherence (34, 35), medication adherence (32, 36), substance use abstinence (37, 38), and smoking cessation (39, 40).

Although existing literature has highlighted that financial incentives may be an effective service engagement strategy for underserved populations, particularly when implemented in the context of a short-term intervention (22, 33, 38), significant knowledge gaps remain. In particular, there is limited evidence on the effectiveness of financial incentives in different populations and settings, including their use in adults experiencing homelessness and mental illness following hospital discharge, a period of high risk for poor health outcomes. In addition, few studies have explored the acceptability of financial incentives, including the perspectives of key stakeholders, such as affected individuals and their service providers. As the use of financial incentives remains controversial, and ethical and pragmatic concerns continue, including concerns about coercion and unintended consequences, further exploration of these issues is warranted (41–44).

To address these knowledge gaps, this article describes an evaluation protocol for a study using mixed methods to investigate the effectiveness of and experiences with using financial incentives to increase engagement of homeless adults with mental illness with a brief case management intervention following hospital discharge in Toronto, Canada. In addition to service engagement, using a pragmatic field trial design, this study will investigate the impact of financial incentives on secondary health, health service use, quality of life, and housing outcomes. Qualitative data, exploring the acceptability, and perceived positive and negative impacts of financial incentives, will be integrated in study findings to support a comprehensive and nuanced understanding of the potential role of financial incentives in supporting service engagement in this underserved population.

## Methods and Analysis

### Program Description

The Coordinated Access to Care for the Homeless (CATCH) program is a multidisciplinary brief case management program for individuals experiencing homelessness and mental illness being discharged from hospital in Toronto, Canada. Informed by the Critical Time Intervention model, the program was launched in 2010 and has been described extensively elsewhere (11, 12, 45–48). Briefly, CATCH aims to support individuals in the critical period following hospital discharge by providing coordinated physical and mental medical care, peer support and intensive case management over a period of 3–6 months. Previous program evaluations have associated CATCH with improvements in mental health and substance use symptoms and health status (11), fewer and shorter hospitalizations, more frequent outpatient psychiatrist visits (46), and continuity of care (45).

### Study Design

Using a community-based, participatory research framework, CATCH-Financial Incentives (CATCH-FI) is a pragmatic field trial using mixed methods to evaluate the impact and acceptability of financial incentives in promoting service engagement of homeless adults with mental illness following hospital discharge. This study was launched in December 2018. Study recruitment is completed, data collection however is ongoing and the trial is registered with ClinicalTrials.gov (Identifier: NCT03770221).

CATCH program participants enrolled in the CATCH-FI trial and randomly assigned to the intervention arm receive $20 for every week they remain meaningfully engaged with program service providers over 6 months of follow-up, or until they are successfully transitioned to longer-term supports. Study participants can earn up to $80CAN per month by attending meetings with their program service provider by phone, text, email, or in-person, as per their care plan. Participants randomly assigned to the control arm receive usual CATCH care, which does not include a financial incentive for attending meetings with their program service provider.

The impact of financial incentives on participants' level of service engagement, measured by program attendance, evaluated as the number of “health-care contacts” a participant makes with CATCH service providers over a 6-month follow-up period. Of note, participant contacts with service providers are counted as “health-care contacts” if they relate to participants' care plans. As a low barrier program, CATCH service providers meet program participants in person, via phone, email, or texts, as per program participants' needs and preferences. Social or trivial contacts of program participants with service providers are not considered “health-care contacts” and are not being measured or documented in program records or reports to program funders.

Secondary health, health service use, quality of life, and housing outcomes (secondary outcomes) are also being collected over the study period. The study hypothesis is that participants receiving financial incentives will have higher levels of service engagement and consequently better health, health service use, quality of life, and housing outcomes compared to participants receiving usual care.

This study additionally uses qualitative methods to investigate stakeholder perspectives and experiences using financial incentives. In-depth qualitative interviews and focus groups were conducted with study participants, program service providers, and other key informants to explore experiences of and perspectives on the acceptability of using financial incentives to support service engagement in this population.

The research questions guiding this study are:

What are the levels of service engagement and health, health service use, quality of life, and housing outcomes for homeless adults with mental health needs receiving financial incentives vs. usual care over a 6-month period following hospital discharge?What are key stakeholder perspectives and experiences using financial incentives, including their acceptability, feasibility, as well as potential drawbacks?

#### Approach to Mixed Methods and Data Integration

Within a community-based, participatory research framework, a convergent mixed methods design is used to evaluate experiences with, perspectives on, and impact of financial incentives on service engagement of an underserved population. With the qualitative sample drawn from the larger study sample, and inclusive of additional key stakeholders, qualitative, and quantitative data collection take place in parallel (49, 50). In addition to integrating qualitative and quantitative data sources through sampling, integration of data sources will take place by comparing and contrasting qualitative and quantitative data once data analysis is completed, and through interpretation and reporting of findings (50–53). Our objective in employing this convergent synthesis approach is to leverage the respective advantages of both types of data to generate a comprehensive and nuanced understanding on how financial incentives may facilitate engagement, health, and well-being of an underserved population, including the range of unique, multi-level contextual factors that may impact implementation of this strategy (50, 54).

### Study Participants: Recruitment, Eligibility, and Randomization

The CATCH program receives 450–600 referrals of homeless adults per year, from hospitals or community agencies, prior to or shortly after hospital discharge for a mental health condition. Study participants were recruited among successive new CATCH program participants. Referrals to the study were made by CATCH staff during program intake meetings. Program participants expressing an interest in receiving information about the study were contacted by research staff to confirm interest, eligibility, to obtain informed consent, and to conduct a baseline assessment.

Study participants meet both CATCH program and CATCH-FI study eligibility criteria. Program eligibility criteria include: (1) current homelessness (defined as having no fixed place to stay for at least the past seven nights with little likelihood of finding a place in the upcoming month) or precarious housing (defined as currently occupying a single room in a multi-tenant building or house with shared common areas including bathroom and kitchen or a hotel/motel as a primary residence, and having a history of one or more episodes of absolute homelessness in the past year); (2) service provider-determined unmet mental health needs; (3) service user-determined unmet support needs; and (4) age 18 years or older. Excluded from the program are individuals with recent aggressive behavior requiring a higher intensity of support, or individuals whose illness severity necessitates residential care. To be eligible for the current study, in addition to meeting program eligibility requirements, participants must have been new referrals to CATCH, recently admitted or readmitted to hospital services, and have had at least one contact with the CATCH team.

Participants were randomized following the baseline interview using block randomization (55), which randomizes the participant list into groups 1:1 using blocks of four and six. This approach has the advantage of maintaining balanced group sizes throughout the recruitment process. The nature of the intervention precluded blinding of participants and study staff.

A subset of participants completing qualitative interviews were purposefully recruited from the larger randomized sample to participate in in-depth semi-structured qualitative interviews. Qualitative study participants were purposefully selected to reflect a diversity of perspectives based on gender, ethnicity, study arm, and service engagement. Study staff invited individuals with the ability to reflect on their experiences, a strategy that has previously been used with success by our team in studies of adults experiencing homelessness and mental illness (11, 12, 45–48). Other key informant stakeholders and CATCH service providers were also purposefully recruited to complete interviews and focus groups based on their role or expertise (health care, health administration, health ethics). Key informants were health and administrative leaders at organizations affiliated with the CATCH program, and had experience serving the target population. CATCH service providers included both case managers and program administrators.

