### Data Collection

Baseline data collection occurred between November 2018 and September 2020; follow-up data collection will be completed in July 2021. All data collection is conducted by trained research assistants from the Survey Research Unit at the Centre for Urban Health Solutions at St. Michael's Hospital. Quantitative surveys lasting 1–2 hwere administered at baseline (up to within 6 weeks of enrollment) and are offered at 6 months post-enrollment (between 6 weeks prior to and up to 16 weeks after that) to all study participants. Survey data are collected using SNAP professional software, and data are held on an internally owned and operated secure sever. All program participants received honoraria paid in-person, by check or email money transfer for each completed interview ($30 for the baseline interview and $60 for the 6-month follow-up interview), in addition to public transportation fare.

Qualitative data collection occurred between April 2019 and December 2020. In-depth, 45–60-min semi-structured interviews were conducted during the study period with program participants and other key informants, and focus groups were conducted with CATCH service providers. Qualitative interview service user participants received an honorarium of $30 and public transportation fare.

This study uses several evidence-based follow-up and study retention strategies for this population (57, 58). To minimize attrition, participants were asked at baseline to provide detailed contact information for themselves and any family, friends, or service providers who could help locate them. To support study retention further, participants were also encouraged to call study staff monthly to update contact information (receiving a $10 honorarium per call). In addition, study staff regularly reach out to participants between interviews to maintain up to date contact records.

A schedule of enrolment, intervention, and assessment is detailed in Figure 1.

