### Measures

#### Quantitative Measures

The primary outcome is service engagement, or program attendance, measured as a count of health-care contacts with CATCH service providers per month over the 6-month period (or until discharge from the program). CATCH service providers record program participant attendance in health care appointments and care planning meetings lasting at least 5 min in participant health records. Eligible health-care contacts include in-person and virtual appointments, as well as care planning conversations through email or text. This definition is consistent with the current program practices and ensures only eligible health-care contacts are recorded and reported to the funding agency. Data on program attendance will be captured at study end through chart reviews by a blinded study staff.

Demographic data and other participant characteristics including residential status and income sources were collected by self-report at baseline. Secondary outcome measures of mental and physical health status, health service use, quality of life, and housing are being collected at baseline and 6 months and a measure of perceived therapeutic working alliance is collected at 6 months. Health service use will also be evaluated using data linkage of administrative health records, conducted at ICES, which holds population-based health and health service use information at the patient level for all Ontarians with health insurance.

See Table 1 for a detailed description of all quantitative measures.

**Table 1 T1:** Description of measures.

**Domain**	**Instrument**	**Description of instrument**

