**Health service use**		
	Self-report	Self-reported number of emergency department visits, hospital admissions, and days in hospital in the past 6 months for pre- and post-randomization.
	ICES administrative data linkage^a^	Number of emergency department visits, hospital admissions, and physician visits in the 12 months pre- and post-randomization.

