**Housing stability**		
	Dartmouth Residential Time-line Follow-Back (RTLFB)	This modified version of the RTLFB (70, 71) has successfully been used in past studies of homeless populations (72, 73). It uses a calendar and prompts to collect detailed information about participants' type of housing and number of days stably housed for specific time periods. A variable representing time spent homeless in the past 6 months in number of days is included as a baseline demographic measure of homelessness. The primary housing outcome of interest from this scale is the number of days stably housed in the past 6 months.

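### The blanket statement that study staff could not be blinded conflicts with the blinded chart review and, as written, leaves the 6-month survey interviewers unmasked, a partly avoidable risk for the interview-based secondary outcomes

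*Protocol article*

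**What the plan says.** Four parts of the protocol article bear on this.

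- **Blinding** (Study Participants: Recruitment, Eligibility, and Randomization): "The nature of the intervention precluded blinding of participants and study staff". The same section says "Participants were randomized following the baseline interview using block randomization", so the baseline survey is completed before any arm exists.
- **Primary outcome** (Quantitative Measures): "Data on program attendance will be captured at study end through chart reviews by a blinded study staff".
- **Survey** (Data Collection): "All data collection is conducted by trained research assistants from the Survey Research Unit". Surveys of 1–2 hours are administered at baseline and again around 6 months. Under Quantitative Measures: "Secondary outcome measures of mental and physical health status, health service use, quality of life, and housing are being collected at baseline and 6 months".
- **Instruments** (Table 1): most are participant ratings or recall, for example "Self-reported number of emergency department visits, hospital admissions, and days in hospital in the past 6 months". The residential follow-back (RTLFB) is described differently: "It uses a calendar and prompts to collect detailed information about participants' type of housing and number of days stably housed".

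Health service use is also taken from ICES administrative linkage. No section gives the blinding status of the survey research assistants separately.

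**The concern.** The reason given for not blinding does not reach everyone it is applied to. A cash payment for attending meetings cannot be hidden from the participant, from the CATCH provider or from whoever pays. It does not by itself disclose anything to an interviewer from a survey unit, and nothing described in the survey instruments needs the arm to be known. The plan already masks one assessor, so masking was thought feasible and worthwhile for the primary outcome.

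At stake are the secondary claims. The hypothesis under Study Design is that incentives lead to better health, health service use, quality of life and housing. Apart from the ICES linkage, the evidence for these comes from the 6-month survey. An interviewer who knows the arm could probe or code differently between arms. Because randomization follows the baseline survey, only the follow-up measurement is exposed. Neither intention-to-treat analysis nor adjustment for baseline removes a shift that enters at follow-up.

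**Working it through.** The protocol gives no figure on blinding, so the check is mainly a comparison of the text.

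**Step 1: is the blanket statement true as worded?** The eligibility and randomization section says the intervention precluded blinding of study staff. Quantitative Measures assigns chart review to a blinded member of study staff, using the same term. The two statements cannot both hold without a qualification that neither gives.

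**Step 2: are the survey interviewers among the study staff?** The article names CATCH service providers separately and uses study staff for research personnel, such as those who keep in touch with participants between interviews. Including the Survey Research Unit assistants is a reasonable reading, but it is an inference.

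**Step 3: does the incentive force the interviewers to be unmasked?** Under Study Design, payment depends on weekly engagement with a program provider. The survey is a separate activity with its own honorarium, and no step described in it depends on arm.

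**Step 4: which outcomes are exposed?**

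| Outcome | Source | Exposure to interviewer knowledge |
|---|---|---|
| Service contacts (primary) | Chart review, blinded reviewer | None |
| ICES visits and admissions | Administrative records | None |
| RTLFB days stably housed | Calendar with interviewer prompts | Most direct |
| CSI, GAIN-SS, SF-36, QoLi-20, EQ-5D-5L/VAS, WAI-SR, self-reported service use | Participant's own answers in the survey | Possible through the way questions are put; the participant's own knowledge of arm remains |

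**Step 5: purely illustrative arithmetic.** The documents give no size for interviewer bias, so every bias below is assumed. The planned total of 172 less 22% attrition is 172 × 0.78 = 134, or 67 per arm, which matches the protocol's figure of 67 per group before inflation. Take 67 interviewed per arm, and an assumed correlation r between baseline and 6 months. The ANCOVA standard error in SD units is √(2(1 − r²)/67). For r = 0.5 this is √(2 × 0.75/67) = 0.150. With no true effect and a shift b, the two-sided 5% rejection probability is 1 − Φ(1.96 − b/SE) + Φ(−1.96 − b/SE).

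- b = 0.1 SD: 10.3% (9.7% to 11.2% for r = 0.4 to 0.6).
- b = 0.2 SD: 26.7% (24.4% to 30.4%).
- Without baseline adjustment, SE = √(2/67) = 0.173, giving 8.9% and 21.2%.

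These figures show what any differential shift of that size would do, whatever its source. They apply to the ANCOVA outcomes (QoLi-20, CSI, SF-36, EQ-5D VAS), which are participant-rated. They do not apply to days stably housed, which is analysed by GEE with a count distribution.

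**The case against.** The strongest reply is that the interviewers' knowledge of arm is inferred. If the blanket sentence already has one unstated exception, the chart reviewer, it may have another. A condensed article may also leave role-by-role masking to the full protocol. The first part stands: a reader might infer that the interviewers know the arm, and no section says so. The second part stands only in part. The article does not merely omit the detail; it states a rule and a reason, and the rule conflicts with its own practice.

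Masking interviewers would also remove only part of the problem. Participants cannot be blinded and most instruments are their own answers, so reporting bias remains and some participants will disclose their arm. This stands. It is why the risk is called partly avoidable, and why the housing measure is singled out as the only one shown to depend on prompting.

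Two further inferences are tempting and unsupported. One is that the secondary outcomes are in fact biased, all in the same direction. The text shows exposure, not bias, and gives no direction. The other is that the trial's false-positive rate is about 10% or 27%. Those values follow from an assumed shift and cannot separate an interviewer effect from participant reporting.

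**Conclusion.** The point holds in a limited form. The blinding sentence contradicts the blinded chart review and gives a reason that does not extend to the 6-month interviewers. Read as written, it leaves them unmasked without need. This exposes the interviewer-administered secondary outcomes, above all RTLFB days stably housed, to a partly avoidable risk of assessor bias. The primary outcome and the ICES outcomes are outside the point, and the baseline survey precedes allocation.

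The conclusion rests on two things: that study staff includes the survey assistants, and that nothing unstated in the survey procedure reveals the arm to them. The size of any bias cannot be derived from the documents, and the percentages in the illustration should not be cited as an estimate. The correction is worth making because it is cheap and because the article describes follow-up as still running, with completion in July 2021.

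**What to change.** Replace the blinding sentence with a statement by role, for example: *Participants and CATCH service providers cannot be blinded. The chart reviewer is blinded to allocation. From the date of this amendment, research assistants conducting the remaining 6-month surveys are not told the allocation.* The dating matters, because an undated statement could be untrue of interviews already done.

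In support:

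- Use the existing research assistants, without giving them the allocation, and open the survey with a short script asking participants not to mention payments.
- Record for every 6-month interview, including completed ones, whether the interviewer knew or learned the arm. Report this descriptively by arm. Do not compare treatments within masked and unmasked interviews: unmasking occurs after randomization and probably depends on arm, since only the incentive group has a program payment to mention, so that comparison could itself introduce bias.
- Optionally, compare self-reported with ICES emergency visits and admissions by arm. Table 1 gives a 6-month window for self-report and 12 months for ICES, so the ICES data must be cut to the same 6 months, anchored to each interview because the survey can fall from 6 weeks before to 16 weeks after the 6-month point. This checks differential reporting in general and cannot isolate an interviewer effect.

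The cost is a short amendment, a script and one recorded item per interview. Some unmasking will occur, and completed interviews cannot be masked. For those, the report should acknowledge the risk.
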